#### Hypotheses

(1):

H-01:CVLT total trials 1–5 after 12 months is not higher in group A than in group BH-11:CVLT total trials 1–5 after 12 months is higher in group A than in group B

(2):

H-02:CVLT short delay after 12 months is not higher in group A than in group BH-12:CVLT short delay after 12 months is higher in group A than in group B

(3):

H-03:CVLT long delay after 12 months is not higher in group A than in group BH-13:CVLT long delay after 12 months is higher in group A than in group B

### Sample Size Estimations and Determination of Sample Size

The following information and assumptions are used for sample size estimations:

Use of data from the study of Andreotti et al. (72) (baseline assessments in healthy women) for group A.Postulation of a 15% change of the mean scores in group A over group B for all 3 primary endpoints (Xgroup A = 1.15 ^*^ Xgroup B).Postulation of a 7.5% change of the standard deviations in group A over group B for all 3 primary endpoints (SDgroup A = 1.075 ^*^ SDgroup B).Type I error (Bonferroni-adjusted) = 0.833% one-sided.Type II error = 20%.Independent samples *t*-test.

#### Results of Sample Size Estimations

The result of the sample size estimation (see Table 3) is a requirement of 48 “valid cases” per group. According to previous work and our clinical expertise we calculated sample size with *n* = 126, expecting a drop out of 15%. As drop-out rates in the literature often show great variety and the applied exercise regime (even though it is highly time efficient and supervised) is rather newly tested within this group, study capacities and all arising costs will be fully covered if we see higher drop-out rates up to *n* = 134 (Assuming a drop-out rate of 20% and considering the possible need for a non-parametric test).

**Table 3 T3:** Sample size estimation.

	**Group B**	**Group A**	**Delta**	**Pooled SD**	** *n* **
CVLT total trials 1–5 after 12 months	48.56 ± 7.47	55.84 ± 8.03	7.28	7.75	2 × 25
CVLT short delay after 12 months	11.02 ± 2.26	12.67 ± 2.43	1.65	2.35	2 × 44
CVLT long delay after 12 months	10.97 ± 2.38	12.62 ± 2.56	1.65	2.47	2 × 48

### Analysis Populations

#### Intent-To-Treat (ITT) Population

All subjects whose study intervention has actually started (group A) or who have reached a time when the study intervention could have started (group B) will be included in the ITT population. All variables will be analyzed.

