### Study Population and Recruitment

Patients are recruited at the department of hematology and internal oncology of the Kepler University Hospital in Linz (AUT). Patients diagnosed with local breast cancer receiving neo-/adjuvant chemotherapy and not fulfilling any exclusion criteria listed in Table 1 are advised by the attending physicians and recruited for study participation. Patients receive a detailed description of the study, can ask any question, and are included in the planned research program only after written consent, according to the ethics committee's approval. Patients can withdraw at any time and for any reason without prejudice to their medical care. Randomization procedures and randomization lists were deposited in a sealed envelope before recruitment of the first patient. Single decoding is available for each subject in sealed envelopes. The envelopes containing information about group affiliation are opened by an authorized study team member at the last possible time (at the earliest after complete baseline evaluation).

**Table 1 T1:** In- and exclusion criteria.

**Inclusion criteria**	**Exclusion criteria**
• Pending chemotherapy (neo-/adjuvant)	• Significant comorbid conditions contraindicating physical activity
• Diagnosed breast cancer	• Cognitive dysfunction, defined by subjective or diagnostic deficits in attention, memory, executive function and/or visual construction before the start of chemotherapy, as well as any known history of cognitive disorder at the baseline screening.
	• In tests without clear ranges of reference values for cognitive impairments in performance, cut-offs will be defined using >1,5 SD from normative data. Cognitive impairment therefore is defined by > 1,5 SD in two tests at baseline assessment.
• Eastern Cooperative Oncology Group (ECOG) performance status of 0 or 1	• Vigorous physical activity of >300 min weekly within the last 6 months before diagnosis of breast cancer (Evaluated by training anamnesis)
• Age ≥ 18–70 years	• Patients unwilling to complete endurance exercise or complete all questionnaires related to the study
• Adequate hematologic function Platelet count > 50 × 10^∧^9/L Hemoglobin > 8 g/dL	• Past or current history of other malignant neoplasms other than breast cancer in the last 5 years
• No motorical dysfunction leading to the disability to perform endurance exercise according to protocol	• Coronary heart disease

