#### Per-Protocol (PP) Population

All subjects without occurrence of any drop-out situation (all valid cases) will be included in the PP population. All variables will be analyzed. The PP analysis is paramount.

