#### Full Analysis Set

All enrolled subjects, that is the ITT population plus subjects whose study intervention has never started (group A) or who don't have reached a time when the study intervention could have started (group B). All variables of all subjects not belonging to the ITT population are analyzed by descriptive statistics, provided that the number of the corresponding subjects is higher than 5, otherwise a narrative presentation of these cases takes place.

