#### Handling of Implausible Values and of Missing Values

Implausible values have to be identified during the data management process in agreement with the clinical investigator. They will be converted into missing values.

Missing values will be replaced only in the ITT population and only for the three primary endpoints. The replacements will be made according to the worst-case principle (use of the worst assessed value in the study).

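### The set labelled intent-to-treat is a modified ITT with different entry rules by arm: women who never start training leave arm A but their counterparts stay in arm B

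*Protocol article*

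**What the plan says.** Under Analysis Populations, the ITT entry in the protocol article reads "All subjects whose study intervention has actually started (group A) or who have reached a time when the study intervention could have started", and this second condition is for group B. The Full Analysis Set is described as "All enrolled subjects, that is the ITT population plus subjects whose study intervention has never started (group A") together with group B women who did not reach the possible start time. For everyone in that set but outside ITT, "All variables of all subjects not belonging to the ITT population are analyzed by descriptive statistics", or a narrative is given if there are five or fewer.

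Three other statements bear on the point:

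- Under Per-Protocol (PP) Population: "The PP analysis is paramount". That set contains only women without any drop-out event.
- Under Handling of Implausible Values and of Missing Values: "Missing values will be replaced only in the ITT population and only for the three primary endpoints". The replacement is the worst value observed in the study.
- Under Study Population and Recruitment, and again under Randomization, the envelope is opened "at the earliest after complete baseline evaluation". The Methods section places the start of exercise in the first week of chemotherapy.

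**The concern.** An ITT analysis protects the comparison only if membership does not depend on anything that happens after allocation and that the arm can influence. Here the two arms have different conditions. In A the woman has to begin the intervention after the envelope has been opened. In B she only has to reach a point in time. The same woman, unwell or reluctant in that first week, is therefore counted in one arm and not in the other.

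What is at stake is the single analysis that a reader would expect to preserve the randomisation. PP does not preserve it, since drop-out, including the rule on consecutive missed HIIT sessions, occurs after allocation. The Full Analysis Set holds all enrolled women, but those it adds are never tested. A superiority trial would then report no test of the randomised groups, while one of its sets carries a name implying that it does.

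**Working it through.** **Entry rules side by side**

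| Situation after the envelope is opened | Arm A | Arm B |
|---|---|---|
| Start time reached, would train | in ITT | in ITT |
| Start time reached, does not or would not train | out; described only | in ITT |
| Start time not reached | out; described only | out; described only |

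Only the middle row differs between arms. The last row shows that B also has a post-allocation exclusion.

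**Inputs.** From Sample Size Estimations and Table 3 of the protocol article: one-sided alpha 0.833% (0.025/3, z = 2.394), power 80%, CVLT long delay difference 1.65, pooled SD 2.47, and 126 women, so 63 per arm.

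**The plan's own figure.** n per group = 2 × (2.394 + 0.842)² × (2.47/1.65)² = 46.9, so 47 by the normal approximation; the exact t calculation gives 49. The stated 48 lies between them, so these inputs are a sound basis. The point disputes no stated number.

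**Size of the selection effect (illustration).** The article gives neither the share p of women who would not start nor the deficit m (in SD) in their 12-month score. Both are assumptions. With no true effect, complete data and no covariate adjustment:

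- bias of A minus B = p × m × SD
- SE = √[SD²/nA + (SD² + p(1−p)(m·SD)²)/63], with nA = 63(1−p)
- one-sided error = 1 − Φ(2.394 − bias/SE)

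For p = 10% and m = 0.5: bias = 0.10 × 0.5 × 2.47 = 0.124 words; SE = √(6.10/57 + 6.24/63) = 0.454; error = 1 − Φ(2.394 − 0.272) = 1.7%.

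| p | m | bias (words) | share of 1.65 | one-sided error |
|---|---|---|---|---|
| 5% | 0.5 | 0.06 | 4% | 1.2% |
| 5% | 0.8 | 0.10 | 6% | 1.5% |
| 10% | 0.5 | 0.12 | 7% | 1.7% |
| 10% | 0.8 | 0.20 | 12% | 2.5% |
| 15% | 0.8 | 0.30 | 18% | 3.9% |

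**With baseline adjustment.** Null ANCOVAs were simulated (6,000–8,000 per scenario, 63 per arm), removing the women least likely to start from A only. The propensity to start had an assumed correlation of 0.3–0.5 with the outcome. At 5–10% non-starting the spurious benefit was 0.02–0.07 SD. Against the planned 1.65/2.47 = 0.67 SD that is about 3–10%. One-sided error across the runs was:

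- 2% non-starting: 0.7–1.2%
- 5%: 0.9–1.7%
- 10%: 1.5–2.8%
- 15%: 1.9–3.9%

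When non-starting was related to outcome only through the adjusted covariate, bias was about zero and error 0.7–1.0%. When the association was reversed, the bias favoured B.

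**Interaction with the worst-value rule.** A never-starter in A is excluded and so never imputed. A comparable woman in B without a 12-month score receives the worst study value. Suppose 5% of each arm is affected and that value lies 2–2.5 SD below the mean (both assumed). The shift toward A is 0.05 × 2 × 2.47 = 0.25 to 0.05 × 2.5 × 2.47 = 0.31 words, or 15–19% of 1.65.

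**The case against.** The strongest reply is that this definition does not drive the main result. PP leads, and never-starters would presumably be absent from it too, so rewriting ITT alone leaves the headline conclusion where it was. That stands, and it limits the severity.

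Second, non-starting may be rare. Table 1 excludes women unwilling to do endurance exercise and those with contraindicating comorbidity, and requires ECOG 0–1. Envelopes are opened as late as possible. Arm A also includes home-based activity, so starting need not mean attending a HIIT session. A 15% non-start rate would equal the entire drop-out allowance. This stands as a limit on size, but it does not make the rule sound.

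Third, the planned ANCOVA adjusts for baseline CVLT, BMI, age, BDI-II, STAI and fatigue, which are plausible reasons for not starting. To the extent that they explain it, the bias disappears. They cannot correct for events after baseline, so the concern remains conditional.

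A reader might infer that exclusions fall on A alone, or that the bias must favour A. The article supports neither. B loses women who do not reach the possible start time, and the direction depends on how non-starters would have scored, on which the article gives no information.

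**Conclusion.** The point holds as a stated rule that breaks the randomised comparison, not as detail left to another document. The set called ITT is a modified ITT, the requirement to have actually started applies to A only, and no planned hypothesis test uses all randomised women as allocated.

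The consequence is conditional. If non-starters would score worse at 12 months beyond what the baseline covariates capture, the ITT comparison leans toward A. At an assumed 5–10% non-start rate the lean is about 0.02–0.07 SD, with one-sided error of about 1–3% against 0.833%. It is close to nominal at 2% non-starting or if the covariates explain non-starting.

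It would be tempting to read those error rates as applying to the trial's primary conclusion. They do not, because ITT is not the leading analysis. On its own this is a should-fix point.

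**What to change.** 1. Define ITT as all randomised participants, analysed in the arm to which they were allocated, whether or not the intervention started. Remove the start condition in A and the time condition in B.
2. Align the Full Analysis Set text so that these women enter the hypothesis tests instead of being only described or narrated.
3. Seek the 12-month CVLT from women who never start. The Drop-Out Procedure asks for measurement at drop-out, which is not the endpoint time.
4. Do not give women without a 12-month score the worst study value by default. If 5–10% of A were never-starters without scores, B were complete and that value lay 2–2.5 SD below the mean, the shift against A would run from 0.05 × 2 = 0.10 SD to 0.10 × 2.5 = 0.25 SD, more than the bias being removed. Use a method such as multiple imputation under missing at random, and keep the worst-value rule as a sensitivity analysis.

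The change has full effect only if this set also replaces PP as the leading analysis.

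Cost: edits to three short sections, some extra follow-up, and dilution of the estimated effect. If non-starters gain nothing and all 63 per arm are assessed, power on long delay is Φ[1.65(1−p)/(2.47√(2/63)) − 2.394]: 0.88 at p = 5% and 0.84 at 10%, falling to 0.79 at 15% and 0.73 at 20%.

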#### Per-Protocol (PP) Population

All subjects without occurrence of any drop-out situation (all valid cases) will be included in the PP population. All variables will be analyzed. The PP analysis is paramount.

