#### Secondary Endpoints

Further neuropsychological related endpoints distinguish by the variable attention and motor-speed, memory, executive functions, and visual construction.

To raise attention and psycho-motoric speed the subtest Digit Symbol Coding (of WAIS IV) is used, in which as fast as possible, symbols shall be written to different objects and the Trail Making Test A, in which numbers shall be put together in the correct order.

Memory function is captured with the subtests Logical Memory I & II (of WMS IV, memorizing texts immediately and after ~30 min). The subtest Digit Span backwards (of WAIS IV), Trail Making Test B/A (quotient of the processing times required for Trail Making Test B) and the “Regensburger-Wortflüssigkeits-Test” for word fluency (words with a special initial letter, words from a special category) measure executive functions.

At last, the subtest Block Design (of WAIS IV) in which patterns have to be recreated from a template with cubes is used to get information about the visual construction.

Secondary endpoints of physical activity and exercise related aspects are represented by performance changes obtained from exercise testing. Main variables are maximal oxygen uptake (VO_2max_) and maximal power output (P_max_), submaximal threshold values such as the first and the second ventilatory thresholds (VT_1_, VT_2_), body composition (body fat, muscle mass, Waist-to-Hip ratio, BMI) and the global physical activity questionnaire (GPAQ).

Additionally morphological changes of the heart will be objectified by strain-analyses. Speckle-tracking-echocardiography performed by Aplio-i900 (Canon) is implemented to evaluate possible chemotherapy related effects on the ventricular function.

Further patient-related endpoints like fatigue, emotional functioning/well-being, physical functioning/well-being, and QOL are measured by the Pittsburgh Sleep Quality Index (PSQI), Multidimensional fatigue inventory (MFI-20), Functional Assessment of Cancer Therapy-General (FACT-G, FACT-G/F), Beck-Depression-Inventar (BDI-II) and State-Trait-Anxiety Inventory (STAI).

Survival related endpoints are defined as the time from randomization to any signs of locoregional or metastatic recurrence or the appearance of secondary cancer or death, whichever occurs first - disease free survival (DFS) and time from randomization to death from any cause - overall survival (OS).

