### Drop-Out Procedure

Patients can quit study participation at any time and for any reason. Except for personal reasons, participation is terminated if participants miss HIIT sessions for more than five weeks in a row. In order to collect sufficient data for statistical analysis, participants are asked to undergo all endpoint measurements at the time of study drop-out.

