#### Regression Analyses

The influence of exercise and exercise test results on overall survival and disease-free survival will be investigated by cox regression analyses. Multiple regression analyses will be used to investigate the influence of baseline characteristics and any specific findings during the intervention phase on the primary endpoints in group A.

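### The per-protocol set leads for every variable, including DFS and OS counted from randomisation, so first-year DFS events can be lost unequally by arm

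*Protocol article*

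**What the plan says.** All references are to the protocol article.

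- **Time origin and events** (Secondary Endpoints): "Survival related endpoints are defined as the time from randomization to any signs of locoregional or metastatic recurrence", with secondary cancer and death also counting for DFS. OS runs from randomisation to death from any cause.
- **PP set** (Per-Protocol (PP) Population): membership is defined by the words "All subjects without occurrence of any drop-out situation (all valid cases) will be included in the PP population. All variables will be analyzed". No exception is made for DFS or OS. Its closing sentence ranks this analysis first: "The PP analysis is paramount".
- **ITT set** (Intent-To-Treat (ITT) Population): membership is defined by the words "All subjects whose study intervention has actually started (group A) or who have reached a time when the study intervention could have started", the last part being for group B. All variables are analysed in this set too.
- **Drop-out** (Drop-Out Procedure): a woman may leave at any time for any reason. Apart from that, "participation is terminated if participants miss HIIT sessions for more than five weeks in a row". Recurrence and death are not named as drop-out situations.
- **Who has HIIT** (Methods; Groups and Description of Intervention): arm A is asked to attend one supervised session a week. Arm B has none.
- **Survival analysis** (Regression Analyses): the stated plan is "The influence of exercise and exercise test results on overall survival and disease-free survival will be investigated by cox regression analyses". No analysis set is named there, nor for the Kaplan-Meier plots under Presentation of the Results.
- **Status** (Type I Error Adjustment): everything outside the three CVLT hypotheses is descriptive.
- **Follow-up** (Data Collection and Timeline/Testing Procedure): 12 months of intervention, then follow-up at 12 and 24 months after its end, using parameters from clinical routine.

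**The concern.** A time-to-event analysis from randomisation should include everyone at risk from randomisation. The PP set instead selects women by a course that unfolds over the following 12 months. For DFS the event can itself cause the exclusion, because a recurrence may interrupt training.

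The written rule is one-sided. Take two women with the same recurrence in month 7. If the arm A woman then misses HIIT for six weeks, she is terminated, is no longer a valid case, and her event leaves the leading analysis. The arm B woman has no session to miss. Unless she chooses to leave, she stays and her event counts.

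For the CVLT, PP selection loses women whose outcome was still to be measured. Here selection can depend on the outcome being analysed. It arises even in a Cox model whose only covariate is the randomised arm. At stake is the direction of the DFS hazard ratio and the shape of the survival curves that will be published as leading results.

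**Working it through.** The article gives no event rate, event target or power for DFS or OS, so there is no survival figure of its own to reproduce. The size has to be shown over a range of assumptions.

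**Inputs from the article:** 126 women allocated 1:1, so 63 per arm; 12 months of intervention plus 24 months, so 36 months in total; termination after more than five weeks of missed HIIT, possible in arm A only.

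**Assumptions:** yearly DFS event rate r of 2, 5 or 10%, constant hazard λ = −ln(1−r), true hazard ratio 1, and stated shares of first-year events removed from the PP set.

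**Step 1: events at stake.** Per arm, first-year events = 63r and 36-month events = 63(1−(1−r)³).

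| r | first year | by 36 months | first-year share |
|---|---|---|---|
| 2% | 1.3 | 3.7 | 34% |
| 5% | 3.2 | 9.0 | 35% |
| 10% | 6.3 | 17.1 | 37% |

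**Step 2: one case by hand (r = 5%, all removable events lost in A, none in B).** λ = 0.0513. An event in about the last five weeks of the year cannot trip the rule before month 12, so the removable window is 47/52 of a year.
- Removable in A: 63(1−exp(−0.0513×47/52)) = 2.85 events, carrying about 1.28 person-years.
- Arm B: 8.99 events in 8.99/0.0513 = 175.2 person-years, rate 0.0513.
- Arm A: 8.99−2.85 = 6.13 events (unrounded inputs) in 175.2−1.28 = 173.9 person-years, rate 0.0353.
- Ratio: 0.0353/0.0513 = 0.69. The large-sample Cox fit gives 0.68.

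With half of the removable events lost in A, the same sum is (8.99−1.43)/(175.2−0.64) = 0.0433, and 0.0433/0.0513 = 0.84, as in the Cox fit.

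**Step 3: range of the expected Cox hazard ratio over r = 2-10%, true value 1.**

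| First-year events removed | 36 months | 24 months |
|---|---|---|
| equally in both arms (all) | 0.99-1.01 | 0.99-1.01 |
| half in A, none in B | 0.84-0.86 | 0.76-0.77 |
| all in A, half in B | 0.77-0.79 | 0.65-0.68 |
| all in A, none in B | 0.67-0.70 | 0.53-0.54 |

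The rows with none removed in B use the 47-week window. The other two rows use the full year.

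**Step 4: consequence at 63 per arm** (log-rank test, two-sided 5%, 36 months, 4,000 simulated trials per setting). Keeping everyone from randomisation, the test rejects in 4-5% of trials, about 2% in favour of A. If every first-year event leaves A and none leaves B, findings in favour of A rise to 6, 12 and 21% at r = 2, 5 and 10%. These three figures remove the whole first year and so slightly overstate that extreme case.

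**Step 5: OS.** A woman who dies before t2 could hardly be a valid case in either arm. If so, removal is equal and the hazard ratio stays near 1.0 (first row of Step 3). About a third of the events is lost, and a curve drawn from randomisation is flat for the first year.

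**The case against.** A reader might infer more than the article supports: that the PP set deletes all first-year recurrences and deaths, mostly in arm A, that survival is decided in that set, and that exercise will look protective on both DFS and OS. Five points stand against that reading.

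1. Neither recurrence nor death is listed as a drop-out situation. For recurrence the route runs through missed HIIT, and whether a given recurrence interrupts training for more than five weeks is not known.
2. Arm B women with a recurrence may also leave, since anyone may quit for any reason. The imbalance therefore has a direction but no known size, and no bias at all is within the range.
3. For OS, equal loss of deaths from both arms leaves the hazard ratio at about 1.0. The bias argument belongs to DFS only.
4. The ITT set also covers all variables, so these events are not lost from the trial's results altogether.
5. DFS and OS carry no confirmatory hypothesis, their results are descriptive, and few events are involved: at 5% per year, about three per arm in the first year.

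It can also be said that this is one consequence of a broader choice, ranking PP above ITT for every variable, and that reversing the ranking would largely cure it. That is fair, but DFS and OS would still need their own statement. The ITT set is restricted to women who started, or could have started, the intervention, so it is not quite all randomised women.

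These points limit the size and the wording. They do not remove the defect: the PP set is ranked first without exception, the Cox section names no other set, and the termination rule can apply to one arm only.

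**Conclusion.** The point holds as a rule that can give a wrong leading result for DFS. The analysis ranked first starts the clock at randomisation, selects on later events, and includes a termination rule that only arm A can trigger. Any resulting imbalance favours exercise.

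Under no true effect, the expected 36-month hazard ratio lies between about 1.0 and 0.67-0.70, with 0.84-0.86 as an intermediate case. These values rest on assumed event rates of 2-10% per year, a constant hazard and assumed removal shares; the article gives none of these. For OS the expected harm is lost events and an artificially flat first year, provided that early deaths are treated alike in both arms. Because the endpoints are secondary and descriptive and an ITT analysis exists, this should be corrected but does not threaten the trial's primary conclusion.

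**What to change.** In Per-Protocol (PP) Population and Regression Analyses, exempt DFS and OS from the statement that ranks the PP analysis first. State that:

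- the leading Kaplan-Meier and Cox analyses of DFS and OS include every randomised woman in her allocated arm, from randomisation to event or last known status;
- drop-out or leaving the exercise programme is neither an exclusion nor an event for these endpoints;
- status after drop-out is taken from the routine clinical follow-up already planned, where consent allows;
- any PP survival analysis is a landmark analysis from t2 among event-free completers, labelled supportive.

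The cost is a short addition to the text. It needs no new visits, no change in sample size and no change to the exercise or termination rules. The small downside is that the estimate then reflects assignment to exercise, including women who stop.

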### Groups and Description of Intervention

#### Exercise Intervention Arm (A)

Participants randomized to the exercise arm are motivated to fulfill the general physical activity recommendations with a defined heart rate and material for strength training (folder and exercise video). The frequency and duration of the home-based exercise depends on individual circumstances but follows general suggestions.

American College of Sports Medicine (ACSM) has recommended the following physical activity for cancer survivors (69):

Take part in regular physical activity.Avoid inactivity and return to normal daily activities as soon as possible after diagnosis.Aim to exercise at least 150 min weekly with moderate intensity.Include strength training exercises at least 2 days per week.

The advised heart rate therefore is defined by the baseline exercise testing and adjusted after 6 months if necessary.

Additionally, group A is asked to perform a supervised HIIT at the Cardiomed Linz rehabilitation center once a week.

The high intensity exercise interventions are performed on a stationary bike (ergo_bike premium 8, daum electronic gmbh, D). An experienced and accredited therapy specialist supervises and supports the exercise interventions throughout the trial.

Participants perform alternating intervals of maximal power output P_max_ (measured by the exercise test) and rest in a ratio of 1:3. The duration of the P_max_ interval is 20 and 60 s for pause.

The HIIT program is set up in two cycles; one includes an enhancement of the weekly intervals and a recovery unit (3:1) (shown in Figure 2A). This cycle is followed by a stabilization cycle (4 weeks), in which the number of intervals is kept constant (shown in Figure 2B). The next cycle starts with a higher number of intervals and is enhanced over 3 weeks, followed by a recovery unit (3:1), and continued by another stabilization cycle (4 weeks). A schematic graphic of this periodized exercise regimen is shown in Figure 2 (71). After 6 months of intervention, a re-evaluation of the patient's performance is conducted as described above. The peak load of the intervals will be adapted according to the new P_max_ if any alteration in peak performance is observed.

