#### Control Arm (B)

Participants in the control arm receive usual care and physical activity recommendations following regular procedures. Patients are examined during clinical visits. The control group receives the same physical activity recommendations (see above) as the intervention group except any heart rate suggestions.

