### Biostatistical Planning and Analysis

#### Concept

The study is based on a superiority approach with a comparison of two kinds of treatment and with three equal-ranking primary endpoints.

Treatment arms:

Treatment arm A: Endurance exercise intervention → group ATreatment arm B: No endurance exercise intervention → group B

Primary endpoints:

(1): CVLT total trials 1-5 after 12 months [-](2): CVLT short delay after 12 months [-](3): CVLT long delay after 12 months [-]

The type I error will be adjusted according to Bonferroni.

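### The per-protocol set decides a superiority trial, and its one protocol-imposed exclusion, missed HIIT, can act only on arm A

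*Protocol article*

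**What the plan says.** Under Concept, the protocol article fixes the objective: "The study is based on a superiority approach with a comparison of two kinds of treatment and with three equal-ranking primary endpoints". Under Per-Protocol (PP) Population it defines the set, "All subjects without occurrence of any drop-out situation (all valid cases) will be included in the PP population", and then ranks it: "The PP analysis is paramount".

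Drop-Out Procedure gives two routes out. One is open to both arms: "Patients can quit study participation at any time and for any reason". The other is imposed by the protocol: "participation is terminated if participants miss HIIT sessions for more than five weeks in a row".

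The arms differ in whether the second route can apply. For the exercise arm, "Additionally, group A is asked to perform a supervised HIIT at the Cardiomed Linz rehabilitation center once a week". For the control arm, "Participants in the control arm receive usual care and physical activity recommendations following regular procedures".

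An intention-to-treat (ITT) analysis is also planned. Its set leaves out randomised participants whose intervention never started (A) or never could have started (B). In that set alone, missing primary values are replaced by the worst value observed in the study (Handling of Implausible Values and of Missing Values).

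**The concern.** In a superiority trial the confirmatory comparison relies on randomisation to make the arms comparable. Here the decisive set depends on what happens after randomisation, and one of the exclusion routes exists in one arm only. A control participant has no HIIT sessions to miss, so the rule cannot remove her.

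This matters if missing HIIT is related to 12-month cognition. Long gaps during a year of neo-/adjuvant treatment could reflect toxicity, fatigue or low mood, and the Introduction itself links depression and fatigue to cognitive impairment. If so, poorer performers leave A while comparable women stay in B. The bias then favours the hypothesis that CVLT scores are higher in A, and a positive result could partly reflect who was excluded.

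**Working it through.** **1. The plan's own sample size.** Inputs from Table 3 and the sample size assumptions: long delay, difference 1.65, pooled SD 2.47, one-sided alpha 0.833% (0.025/3), power 80%.

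n per group = 2 × SD² × (z_α + z_β)² / δ² = 2 × 2.47² × (2.394 + 0.842)² / 1.65² = 46.9, so 47. The exact t calculation gives 49 and the plan states 48. The figure reproduces, and it counts valid cases, that is, the PP set.

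**2. What the documents do not give.** Drop-out is stated as 15% (n = 126) or 20% (n = 134), not split by arm. No correlation between drop-out and outcome is given. Both are assumptions below.

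**3. Size of a spurious difference with no true effect.** Take 63 randomised per arm. Let retention depend on a latent tendency correlated ρ with the 12-month score. If a fraction q of an arm is retained, its mean rises by about ρ × φ(z_q)/q SD, where z_q is the normal quantile of q.

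Example: A loses 15% (54 of 63 kept, q = 0.857), B loses none, ρ = 0.3.
- Shift = 0.3 × 0.263 = 0.079 SD.
- Standard error = √(1/54 + 1/63) = 0.185 SD.
- Type I error ≈ Φ(0.079/0.185 − 2.394) = Φ(−1.97) = 2.4%, against the nominal 0.833%.

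Simulated one-sided type I error per endpoint, for ρ = 0.3 and ρ = 0.5 (– means not run):

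| Lost A / B | Average loss | Unadjusted t-test | Adjusted for baseline score (assumed r = 0.5) |
|---|---|---|---|
| 15% / 15% | 15% | – | 0.8%; 0.6% |
| 20% / 10% | 15% | – | 1.5%; 2.2% |
| 15% / 5% | 10% | 1.7%; 2.7% | 1.5%; 2.4% |
| 15% / 0% | 7.5% | 2.4%; 4.7% | 2.0%; 4.4% |
| 20% / 0% | 10% | – | 2.6%; 5.3% |
| 25% / 5% | 15% | 3.1%; 6.5% | 2.2%; 4.8% |

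At ρ = 0 the error stays near 0.8% whatever the split. In the unadjusted runs shown, the spurious difference runs from 0.048 SD (15%/5%, ρ = 0.3) to 0.162 SD (25%/5%, ρ = 0.5). On long delay that is 0.12 to 0.40 words, against a planned 1.65.

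**4. Power if all randomised participants are analysed and their outcomes observed.** Power = Φ(δ / (SD × √(2/n)) − 2.394), with n = 63 and standard error 2.47 × √(2/63) = 0.440.
- No dilution: 1.65/0.440 = 3.75, power 91%.
- Effect diluted 15% by non-adherence: 1.40/0.440 = 3.19, power 79%.
- Diluted 20%: 1.32/0.440 = 3.00, power 73%.
- Diluted 25%: 1.24/0.440 = 2.81, power 66%.

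With 67 per arm the figures are 93%, 81%, 76% and 69%.

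**5. Power if the worst-value rule is kept.** Simulation with the Table 3 SDs for long delay and 63 per arm. With 15% of A and 5% of B missing, the rule moves the difference by about −0.6 words under no effect and leaves about 14% power at the planned effect. With 15% missing in both arms, power is about 51%.

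**The case against.** A reader might infer that selected completers in A are compared with nearly all of B. The documents do not support that. Participants in B may leave at any time, any drop-out removes them from PP, and the stated drop-out rate is not split by arm. What is supported is that A has one extra exclusion route, based on attendance.

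A reader might also infer that the women with the worst prognosis are necessarily the ones removed. The documents do not say why sessions would be missed. Better-functioning women who return to work could miss them too, which would push the bias the other way. The direction is therefore plausible, not shown.

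The size is open as well. Scenarios with no loss in B average below the planned 15%. Of the two unequal splits in the table that average 15%, 20%/10% gives modest inflation and 25%/5% gives more. The rule is also lenient: attending every sixth week never exceeds a five-week gap, so 8 of 52 sessions would pass (52/6, rounded down), and losses driven by the rule alone may be small.

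Two features of the plan mitigate. The covariates include the baseline CVLT score, BDI-II, STAI and fatigue, which may reduce the bias but cannot remove selection on the course after randomisation. The ITT analysis with worst-value imputation would work against A if A has more missing data, so a PP artefact would stand beside a conservative result. However, the plan ranks PP first, so ITT does not decide the trial.

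**Conclusion.** The point holds as a matter of design. The protocol makes a set decisive whose one protocol-imposed exclusion can act on arm A only, in a trial meant to show superiority. That rests on the text alone and needs no assumption.

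The size and direction of the bias do rest on assumptions. With no correlation between loss and outcome, or with equal loss in both arms, the type I error per endpoint stays at about the nominal 0.8%. With ρ of 0.3 to 0.5 it is about 1.5% to 2.2% at 20%/10%, and roughly 2% to 6% when A loses 15% to 25% and B none to 5% (as low as 1.5% at 15%/5%). The bias favours A only if poorer performers are the ones who miss HIIT.

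The hierarchy should be changed before analysis. Simply promoting the ITT set as defined would not be enough, because it omits never-starters and carries the worst-value rule. The five-week rule is not judged here as a rule for managing participants, only for its use in defining the decisive set.

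**What to change.** Replace the sentence "The PP analysis is paramount" with: The confirmatory analysis of the three primary endpoints includes all randomised participants, analysed as randomised, including those who never started the intervention; the per-protocol analysis is supportive.

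Make two further changes at the same time:

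- **Outcome collection.** Ask participants who stop HIIT or drop out for the 12-month CVLT as well as the measurement at drop-out. Drop-Out Procedure currently requests only the latter.
- **Missing data.** For this analysis, replace worst-value imputation with a likelihood-based method or multiple imputation. Keep the worst-value rule as a sensitivity analysis.

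Restate the power for the new primary set, since the present calculation counts valid cases only.

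The cost is a few sentences, an amendment, one further CVLT request to participants who stop, and a smaller expected effect because non-adherent participants are included. No new participants are needed if dilution is slight. At 15% dilution 63 per arm falls just below the planned 80% power; at 25% dilution even 67 per arm reaches only 69%.
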